### Sample size

The sample size was calculated to detect a minimum clinically important difference of 10 points^24^ (on a 0–100 standardised AUC scale for pain) between allocated groups over the first 3 days postrandomisation. Assuming a SD of 30 points (a conservative estimate based on previous cellulitis trials and meta-analyses),^12 14 25^ 191 participants per group with primary outcome data are needed for 90% power at a two-sided 5% statistical significance level. To account for up to 15% of participants not returning sufficient pain scores to derive the primary outcome (baseline pain score plus at least one more pain score at least 24 hours later), the recruitment target is 450 participants (225 per group). The sample size was calculated using PASS sample size software. The SD estimate will be reviewed, blinded, at the end of the internal pilot phase.

### Recruitment

Potential participants will be identified and screened by local research teams or clinicians on presentation to a participating urgent secondary care site. This will be completed via review of medical records and discussion with the potential participant, as needed. If potentially eligible, they will be invited to review the participant information materials and, if they are interested, to provide their informed consent to participate.

Final eligibility will be confirmed by the local site principal investigator or an appropriately qualified and delegated clinician (registered prescriber with appropriate clinical experience). If the potential participant is of childbearing potential, they will be required to complete a pregnancy test before final eligibility can be confirmed.

Efforts to ensure inclusive recruitment include selecting participating sites to cover underserved geographical areas, recording any language barriers during the internal pilot phase to identify needs for translation of key documents (PIS, video subtitles), and specific funding for sites to support recruitment of people who inject drugs, an underserved population with high rates of skin infection.

Efforts have been made to minimise staff and participant burden to encourage recruitment in an urgent secondary care setting by minimising data collection as far as possible and designing all follow-up to be remote, negating the need for additional in-person visits for the trial.

### Randomisation: sequence generation, allocation concealment mechanism and implementation

Randomisation will be stratified by recruiting site and then minimised using an algorithm with a random element to balance allocated groups on three factors:

Prior antimicrobial therapy for this current episode of cellulitis (yes/no)Diabetes status (defined by a known diagnosis of either type 1 or type 2 diabetes mellitus, yes/no)Severity of cellulitis (Eron class 1 vs all other classes).

Eligible, consented participants with minimum baseline data collected will be randomised 1:1 to either dexamethasone or placebo. Randomisation is carried out via a secure 24-hour web-based randomisation service provided by the Centre for Healthcare Randomised Trials (CHaRT, University of Aberdeen). Randomisation will be completed by a delegated member of the site team or (in case of technical issues at site) may be conducted by ExeCTU staff on direction from a delegated member of the site team.

A master list of pack IDs will be produced by the senior (unblinded) statistician and provided to CHaRT for upload into the randomisation system and to the Investigational Medicinal Product (IMP) manufacturer for labelling of packs. The master list will indicate which packs contain placebo and which contain dexamethasone.

The CHaRT system will be integrated into the main study database (REDCap) so that randomisation can be initiated from within REDCap. Once the online randomisation process is complete, REDCap will indicate to the user a blinded pack ID which should be dispensed to the participant; it will not indicate whether the participant has been allocated to receive IMP or placebo. All site staff (and any central trial staff who may assist sites with randomisation) will be blinded to allocation and will not have any access to the master list of pack IDs or allocation sequence.

### Blinding

The trial is double-blind; participants and site research teams (clinicians, data collectors and outcome assessors) will be unaware of treatment allocation. This is achieved by the IMP manufacturer providing identically appearing over-encapsulated IMP (each containing a 4 mg dexamethasone tablet with backfill) and matching placebo capsules, packaged and labelled with blinded pack IDs. Inability to take oral medication is listed as an exclusion criterion to prevent participants or staff becoming accidentally unblinded by opening the capsules to administer the intervention.

Access to the master list linking pack IDs to treatment allocation will be restricted to the senior (unblinded) statistician, the IMP manufacturer, developers of the randomisation system (CHaRT) and unblinded members of the ExeCTU team as required for their role. The randomisation system will be fully tested prior to go-live to ensure the adequate concealment of allocation. Analysing trial statisticians will remain blinded until the primary statistical analysis of the primary outcome is complete.

Emergency unblinding will be available 24/7 via a dedicated automated phoneline in case clinically necessary for the medical management of a participant. The decision to unblind rests with the treating clinician. Unblinding events will be documented and reported.

### Data management

ExeCTU will oversee the day-to-day management of participant data according to a trial specific Data Management Plan (DMP). Work instructions and ongoing training will be provided to recruiting site teams on record keeping and data entry processes.

All screening, baseline and outcome data for the trial will be entered into an electronic data capture system (EDC; REDCap Academic), hosted by University of Exeter and managed by ExeCTU following UK General Data Protection Regulation. Trial-specific eCRFs will be created, including validation and range checks at the point of data entry. Data will be entered into the eCRFs via a combination of SMS and online surveys to participants, and entry into the database by site staff. Full testing of the EDC will be conducted and documented before starting recruitment.

Access to REDCap Academic for the trial will be managed using password-protected individual user accounts. Each account will be restricted by site, functionality and data as appropriate for the person’s role. REDCap Academic also maintains electronic audit trails to ensure data integrity and security. Access will be granted to authorised representatives from the North Bristol NHS Trust as Sponsor, as well as representatives from University of Exeter and regulatory agencies, for example, MHRA, if required for the purposes of auditing, monitoring and inspection of the trial.

The essential documentation will be archived for a minimum of 10 years after the end of the trial. After 10 years, all personal identifiable data (PID) will be securely destroyed on authorisation from the Sponsor. The anonymised data set will be stored indefinitely for the purposes of future ethically approved research.

### Statistical methods

A detailed Statistical Analysis Plan (SAP) will be written following Gamble *et al*^26^ guidelines, approved by an independent statistician, and made publicly available before the trial follow-up period concludes. Any amendments to the SAP will be documented. Results will be reported following the CONsolidated Standards Of Reporting Trials (CONSORT) statement and relevant extensions (e.g., for Patient Reported Outcomes, Pragmatic Trials). Emphasis will be on estimation rather than hypothesis testing; tests will be at the 5% two-sided level. Baseline characteristics will be summarised descriptively overall and by allocated group (means/SDs or medians/IQR for continuous; Ns/% for categorical), with no formal between-group testing of baseline data. A CONSORT flow diagram will illustrate participant flow.

The primary analysis population will be all randomised participants who contribute at least two out of a possible seven pain scores, with the second pain score being at least 24 hours after the baseline pain score. The primary outcome (pain AUC, standardised 0–100) will be analysed using a mixed-effects linear regression model, adjusting for baseline pain, age, sex and the minimisation variables (severity of cellulitis (Eron stage^27^ 1 vs all other stages), antimicrobial therapy for this episode prior to attending urgent secondary care, diabetes status) as fixed effects, and recruitment site as a random effect to account for potential between-site heterogeneity. The adjusted difference in means (and 95% CI) between dexamethasone and placebo groups will be reported; unadjusted difference will also be reported. The primary estimand addresses the effect of dexamethasone plus usual care versus placebo plus usual care, with a treatment policy strategy for intercurrent events. Missing pain scores for the primary outcome will be imputed using linear interpolation if scores are available on either side; if final scores are missing, last observation carried forward (a conservative approach) will be used. Sensitivity analyses will explore other imputation methods (e.g., multiple imputation using chained equations including allocated group, baseline score, centre, minimisation variables, age, sex and predictors of missingness). If an imbalance in baseline characteristics thought to be predictive of outcome is noted, the analysis will be repeated adjusting for these.

Secondary continuous outcomes (PGI-I, pain at 14 days) will be analysed using mixed-effects linear regression models if assumptions are met; PGI-I at days 1, 2 and 3 will use a mixed-effects repeated measures model. Alternative modelling (eg, mixed-effects ordinal logistic models, dichotomisation for logistic regression) will be considered if assumptions are not met, detailed in SAP. Dichotomous secondary outcomes (additional antibiotic use, (re)admission, unscheduled healthcare use, recurrence) will be analysed using mixed-effects logistic models (if event numbers allow). All models will adjust for the same factors as the primary analysis. Adjusted differences in means or ORs (with 95% CIs) will be reported, along with unadjusted estimates.

Descriptive analysis will cover compliance, analgesia details, antibiotic details and dexamethasone-related complications. The estimands framework for secondary outcomes will mirror the primary outcome. Multiple imputation may be considered for missing secondary outcome data. SAEs will be reported descriptively by whether the first dose was taken (not intention to treat (ITT)).

Exploratory subgroup analyses on the primary outcome (not powered for) will be pre-specified for: cellulitis location (lower limb vs other) and NSAID usage at randomisation (user vs non-user). The primary analysis model will be refitted including an interaction term between treatment and the subgroup of interest; minimum numbers for these analyses will be pre-specified in the SAP.

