Oral corticosteroids are well-established anti-inflammatory agents shown to be effective in numerous other acute infectious and inflammatory conditions to dampen the immune response and improve short-term symptoms. For example, systematic reviews have shown benefits of adjunctive corticosteroids in conditions like sore throat and in croup.^10 11^ Two previous randomised trials have investigated corticosteroids for acute cellulitis. One Danish trial (n=112) found that prednisolone (30 mg daily, reducing over a week) significantly reduced time to clinical cure compared with placebo (10.0 vs 14.6 days, p<0.01), with no evidence of increased recurrence of cellulitis at 1 year follow-up.^12 13^ An unpublished trial (NCT01671423, n=25) reported a non-statistically significant trend towards greater pain reduction at 48 hours with a single dose of 60 mg prednisolone versus placebo (mean change from baseline 39.9 vs 30.5 points on a 0–100 Visual Analogue Scale). Additionally, trials of non-steroidal anti-inflammatory drugs (NSAIDs), which may have a similar mechanism of action to corticosteroids, have suggested a benefit in cellulitis.^14^ However, there are concerns about the adverse effects of NSAIDs, and so these were not considered in this trial. Current guidelines from the Infectious Diseases Society of America (IDSA) acknowledge the potential for corticosteroids for the treatment of cellulitis but call for further high-quality randomised controlled trials to establish the role of corticosteroids in cellulitis management, a position also echoed by Cochrane.^15 16^

The DEXACELL trial is designed to address this evidence gap. It is a pragmatic, multicentre, double-blind, placebo-controlled, randomised, parallel group, phase 3 superiority trial with an internal pilot phase and a parallel health economic evaluation.

The primary research question is: *Is the addition of oral dexamethasone to usual care in patients who present to urgent secondary care with cellulitis effective and cost-effective in terms of reducing pain, improving quality of life and reducing further antimicrobial usage and healthcare utilisation?* Given the high incidence of cellulitis, even a modest improvement in symptoms and/or a reduction in healthcare costs could have significant population-level benefits.

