#### Usual care

All participants will receive usual care for cellulitis as per local policy at each site, including clinical assessment, antibiotics and analgesia, hospital admission if required, advice on management of concomitant conditions and expected symptom duration. Details of any antibiotics and analgesia administered will be recorded at baseline and at day 14 follow-up.

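### NSAID use at randomisation could be pre-specified as a covariate in the primary pain model: a small, nearly free gain in precision, not a correction of an error

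*Protocol article*

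**What the plan says.** All references are to the protocol article; the SAP is not at hand.

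- **Primary model (Statistical methods).** A mixed-effects linear regression of the standardised pain AUC, "adjusting for baseline pain, age, sex and the minimisation variables", with recruiting site as a random effect. The minimisation variables are cellulitis severity, prior antimicrobial therapy and diabetes. The same adjustment set is carried into the secondary models.
- **Randomisation.** Stratified by site and minimised on those three factors. NSAID or other analgesic use is not among them.
- **Recording (Usual care, and Table 2).** "Details of any antibiotics and analgesia administered will be recorded at baseline and at day 14 follow-up". Under Data collection methods, baseline items outside the minimum dataset may be completed after randomisation but before the first dose. Analgesia is outside that minimum dataset.
- **Background and rationale.** NSAIDs are described as drugs "which may have a similar mechanism of action to corticosteroids, have suggested a benefit in cellulitis".
- **Subgroups (Statistical methods).** "NSAID usage at randomisation (user vs non-user") is one of two exploratory, unpowered subgroups. It is analysed by refitting the primary model with a treatment-by-subgroup interaction, subject to minimum numbers left to the SAP.
- **Imbalance rule (Statistical methods).** If a baseline characteristic thought to be prognostic is seen to be unbalanced, the analysis is repeated with adjustment for it.

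**The concern.** By the article's own account, NSAIDs may act on the process that drives the primary outcome. Use at randomisation is a baseline variable, the trial collects it before dosing, and it matters enough to be one of only two subgroups. The model already includes age and sex, which are not minimisation factors, so the sponsor accepts prognostic covariates beyond the design variables. Leaving this one out is a stated choice, because the covariate list is given in full.

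Two things are at stake, both modest. First, any outcome variance explained by NSAID use, beyond what baseline pain and the other covariates capture, stays in the error term. Second, the only stated route by which NSAID use can enter the overall treatment estimate is the imbalance rule. In the article that rule depends on the data and names no variables and no threshold. The subgroup refit is a different analysis: it asks whether the effect differs by NSAID use and is not planned as an NSAID-adjusted overall estimate. Where a prognostic variable can be foreseen, naming it in advance is better than leaving its use to a judgement made once the baseline table is available.

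**Working it through.** **Inputs from the document (Sample size).** "a minimum clinically important difference of 10 points" on the 0–100 AUC scale; "Assuming a SD of 30 points"; "191 participants per group with primary outcome data are needed for 90% power at a two-sided 5% statistical significance level". The allowance for insufficient pain scores is 15%, giving a target of 450.

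**Inputs that are assumptions.** The document gives neither the proportion p using NSAIDs at randomisation nor the shift g in AUC associated with use. I take p = 0.1 to 0.5 and g = 5 to 15 points, with p = 0.3 and g = 10 as a central case.

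**1. The plan's own figure.** Normal approximation: n = 2 × (1.96 + 1.2816)² × 30² / 10² = 189.1, so 190 per group. With the noncentral t distribution, power is 0.8999 at 190 and 0.9013 at 191, so 191 is right for a two-sample t-test. Total: 382 / 0.85 = 449.4, so 450. The plan's figures reproduce.

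**2. Precision gained by adding the covariate.** Variance share R² = p(1−p)g²/30². Adjusted SD = 30 × √(1−R²). The n and power below use the normal approximation.

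| p, g (assumed) | R² | Adjusted SD | n per group for 90% | Power at 191 per group |
|---|---|---|---|---|
| no NSAID term | – | 30.00 | 190 | 90.28% |
| 0.1, 5 | 0.09 × 25/900 = 0.25% | 29.96 | 189 | 90.35% |
| 0.3, 10 | 0.21 × 100/900 = 2.3% | 29.65 | 185 | 90.93% |
| 0.5, 15 | 0.25 × 225/900 = 6.25% | 29.05 | 178 | 91.99% |

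The gain is therefore between about 0.1 and 1.7 percentage points of power. The 95% CI half-width goes from 1.96 × 3.07 = 6.02 points to between 6.01 and 5.83.

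**3. Overlap with baseline pain.** These figures ignore the covariates already in the model. Part of any effect of analgesia already taken will show in the baseline score, which lowers g. Adjustment also lowers the residual SD, so the starting power is higher. If the residual SD were 25 (assumed), power at 191 per group without the NSAID term is 97.44%. With it, power is 97.48%, 97.81% and 98.37% for the same three rows, a gain of under 1 point throughout.

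**4. Size of a chance imbalance.** The 95% limit for the difference in NSAID use between arms is 1.96 × √(2p(1−p)/191), which is 6.0 percentage points at p = 0.1 and 10.0 at p = 0.5. Multiplied by g, this moves the difference in means by 0.060 × 5 = 0.3 points to 0.100 × 15 = 1.5 points. The treatment standard error is 30 × √(2/191) = 3.07 points and the target difference is 10. The shift is one component of that standard error, so the reported interval already allows for it.

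**5. Validity without the covariate.** In simulations of the comparison without the NSAID term (191 per arm, SD 30, p = 0.3, 20,000 runs each), mean bias was 0.02 points for g = 10 and 0.01 for g = 15. Type I error was 0.048 and 0.051. Neither differs from nominal in any way that matters.

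**The case against.** The strongest case against is that nothing here is wrong. The article fixes a standard covariate set, and using a variable for an exploratory subgroup does not oblige anyone to adjust for it. Baseline pain already absorbs some of the effect of earlier analgesia. The size of the benefit rests on assumed inputs. The looseness of the imbalance rule is a general matter that the SAP may tighten. All of this stands, and it is why the point is an optional improvement.

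Four stronger readings are tempting, and the document does not support them:

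- *The omission biases the primary result.* Randomisation protects the comparison, and the simulations show no bias and no inflation of type I error.
- *NSAID use is dealt with only if an imbalance is noticed.* The interaction refit is pre-specified whatever the balance, subject to minimum numbers. The narrower statement holds: the imbalance rule is the only stated route into the overall estimate.
- *The protocol names NSAID use as a likely effect modifier.* It says NSAIDs may share a mechanism and have suggested a benefit, and it lists the subgroup as exploratory and unpowered. Candidate effect modifier is as far as the text goes.
- *The imbalance rule produces two rival primary estimates.* One primary model is defined and the repeat is additional. The trigger is the baseline data, not the outcome, and the analysing statisticians stay blinded until the primary analysis is complete.

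What survives the objection is that the variable is specific, foreseeable, collected before dosing and already defined for another analysis. Pre-specifying it costs almost nothing.

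**Conclusion.** The point holds as a minor suggestion. The primary model omits a pre-dose variable that the article itself gives reason to think prognostic. The sample size, type I error, estimand and validity of the model are all unaffected. What is forgone is up to about 1.7 percentage points of power at 191 per group if 10% to 50% use NSAIDs and use shifts the AUC by 5 to 15 points, and probably less once baseline pain is in the model. Those two ranges are assumptions; the direction of the association is also unknown, since users may differ in severity. The second benefit cannot be put in numbers: one foreseeable variable would no longer depend on a judgement about observed imbalance.

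**What to change.** Before unblinding, state in the SAP that NSAID use at randomisation (yes/no) is a fixed effect in the primary model and in the models that use the same adjustment set. At minimum, make it a named sensitivity analysis of the primary outcome, run whatever the observed balance. Use the identical variable in the subgroup interaction model. Minimisation need not change.

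The costs are small but should be acknowledged:

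- **One extra covariate, which must be complete.** It is outside the minimum pre-randomisation dataset, so add a completeness check and a stated rule for missing values, so that no participant drops out of the primary analysis because of this field.
- **Logistic secondary models.** Adding a prognostic covariate changes the meaning of a conditional odds ratio slightly. The linear primary model has no such issue: the adjusted difference in means estimates the same quantity. If event numbers are low, the term can be kept to the linear models.

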### Outcomes

#### Primary outcome

Total pain experienced over the first 3 days postrandomisation.

Total pain will be calculated using the standardised area under the curve (AUC) approach from seven individual pain scores, measured using a 0–10 Numerical Rating Scale (NRS) (see wording in online supplemental file S2). The first (baseline) pain score is collected in person prerandomisation as part of a participant questionnaire pack. The remaining six scores are collected postrandomisation at approximately 12-hour intervals (around 8 am and 8 pm) via SMS survey (hereby referred to as timepoints 1–6 (T1–T6)). Actual time of response will be recorded. Alternative methods to collect pain scores (in-person, telephone) are available if SMS is not feasible, depending on staff capacity.

Total pain was chosen as the primary outcome after extensive Patient and Public Involvement (PPI) work. Reduction in erythema has previously been used as a cellulitis outcome measure by regulators,^18^ but was not chosen in this trial for multiple reasons. First, patient feedback was that pain and symptoms were much more important than the size of the erythema. Second, measurement of erythema might be biasing against those of skin of colour. Pain was identified as a key issue for patients with cellulitis, aligning with recent priority setting partnerships.^19^

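### The primary analysis carries the last pain score forward and calls this conservative, but the direction of the bias depends on the course of pain and on which arm stops replying

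*Protocol article*

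**What the plan says.** The primary outcome is a standardised AUC (0–100) built from a baseline score and six later ones. Under Primary outcome: "The remaining six scores are collected postrandomisation at approximately 12-hour intervals". T1 falls at the first 8 am or 8 pm after randomisation (Participant timeline).

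Statistical methods sets two filling rules for the primary analysis. For gaps between replies: "Missing pain scores for the primary outcome will be imputed using linear interpolation if scores are available on either side". For gaps at the end: "if final scores are missing, last observation carried forward (a conservative approach) will be used". Other methods appear only in a supporting role: "Sensitivity analyses will explore other imputation methods (e.g., multiple imputation using chained equations", with a list of predictors that includes allocated group and predictors of missingness.

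Few data are needed to enter the primary analysis. Statistical methods asks for "at least two out of a possible seven pain scores", and Sample size describes the same minimum as "baseline pain score plus at least one more pain score at least 24 hours later".

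Two statements in the Background bear on the expected course of pain. An unpublished 25-participant trial of another corticosteroid reported a "mean change from baseline 39.9 vs 30.5 points" (corticosteroid versus placebo, 0–100 scale, 48 hours). The Background also says that inflammation may persist or get worse over the first 48 to 72 hours.

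**The concern.** Carrying a score forward assumes that pain stops changing when replies stop. The stated estimand follows a treatment policy strategy, so its target is the pain participants actually go on to have. Where pain is still falling, the rule inflates the AUC of early stoppers, and the difference between arms then moves according to which arm has more of them. The word conservative promises a bias towards no effect, and the rule cannot promise that.

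The filled portion can be large. A participant with only baseline and T3 has 36 of the 60 to 72 hours up to T6 set to one value, that is 50% to 60% of the window. The 15% allowance in the sample size and the pilot criterion of at least 85% calculable outcomes count only participants with no calculable AUC. Neither limits how often scores are carried forward. The filled values also enter the model as if observed, so the standard error carries no allowance for imputation.

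At stake is the headline estimate. If replies stop unequally, a positive result could be defended as conservative when the rule had in fact helped it.

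**Working it through.** **Plan's own figure.** For a difference of 10, SD 30, two-sided 5% and 90% power, the noncentral t gives power 0.8999 at 190 per group and 0.9013 at 191, so 191 is reproduced. 382/0.85 = 449.4, which gives 450. This point does not alter the sample size.

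**Inputs from the article.** 48-hour falls of 39.9 (corticosteroid) and 30.5 (placebo); 12-hour spacing; target difference 10; SD 30; 191 per group.

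**Assumptions, not in the article.** Pain falls linearly; T1 is 6 h after randomisation, so T3 = 30 h, T4 = 42 h and T6 = 66 h; stopping is unrelated to a participant's own pain; the share with missing final scores is set by scenario.

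**Overstatement per participant.** With a fall of s points per hour and a gap of g hours from the last score to T6, the excess is a triangle: B = 0.5 × s × g² / 66.

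| Last score | g (h) | Placebo, s = 30.5/48 | Dexamethasone, s = 39.9/48 |
|---|---|---|---|
| T3 | 36 | 0.5 × 0.6354 × 1296/66 = 6.2 | 0.5 × 0.8312 × 1296/66 = 8.2 |
| T4 | 24 | 0.5 × 0.6354 × 576/66 = 2.8 | 0.5 × 0.8312 × 576/66 = 3.6 |

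If pain instead levels off at 48 h, the excesses at 42, 54 and 66 h after a last score at T3 are 12s, 18s and 18s. The trapezoid area is 72s + 180s + 216s = 468s. Divided by 66, this gives 4.5 (placebo) and 5.9 (dexamethasone).

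**Bias in the treatment difference (dexamethasone minus placebo; negative favours dexamethasone).** Bias = p_dex × B_dex − p_plc × B_plc, where p is the share with missing final scores. With these falls the sign changes when p_plc/p_dex = B_dex/B_plc = 39.9/30.5 = 1.31.

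With the last score at T3, the true difference is −0.5 × (9.4/48) × 66 = −6.5, and:

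| Missing dex / placebo | Bias | Direction |
|---|---|---|
| 20% / 20% | 0.2 × 8.16 − 0.2 × 6.24 = +0.4 | attenuated |
| 30% / 10% | 0.3 × 8.16 − 0.1 × 6.24 = +1.8 | attenuated |
| 10% / 20% | 0.1 × 8.16 − 0.2 × 6.24 = −0.4 | exaggerated |
| 10% / 30% | 0.1 × 8.16 − 0.3 × 6.24 = −1.1 | exaggerated |

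**No true effect.** Let both arms fall by the average, (39.9 + 30.5)/2 = 35.2 in 48 h. Then B = 0.5 × (35.2/48) × 1296/66 = 7.2, and SE = 30 × √(2/191) = 3.07. Type I error = Φ(−1.96 + b/SE) + Φ(−1.96 − b/SE), where b is the bias.

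- 10-point gap in missingness: b = 0.72, b/SE = 0.23, type I error 5.6%.
- 20-point gap: b = 1.44, b/SE = 0.47, type I error 7.6%.

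**Worsening pain.** If pain rises, B is negative. Excess stopping on placebo then works against dexamethasone, and sufficient excess stopping on dexamethasone favours it. The arms swap roles, so again no single direction holds.

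**The case against.** The case for leaving the rule alone has weight. The trial is blinded with identical capsules, and telephone or in-person collection is available where SMS is not feasible, so a large imbalance in replies is not the expected outcome. With equal missingness and a faster fall on dexamethasone, the rule does attenuate. So it does if dexamethasone participants stop replying because they feel better. Multiple imputation is already planned, so dependence on the rule would be visible. All of this stands, and it limits the size of the problem. It does not make the label correct as a general statement, and a sensitivity analysis does not change the headline estimate.

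Four stronger readings are tempting and are not supported.

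- A reader might infer serious inflation of type I error, say 7% to 11% from a small bias, on the ground that baseline adjustment shrinks the SE to about 1.1. That needs a residual SD of 1.1/√(2/191) = 10.7, or 11.7 with 225 per group. Against SD 30, covariates would have to explain 85% to 87% of the variance, and nothing in the article gives this.
- Larger figures (8.8% to 11.9% for a 20-point gap) follow if every incomplete participant last replied at 24 h. T2 falls 12 to 24 h after randomisation, so it normally comes too early to qualify, and T3 is the usual earliest qualifying score.
- A reader might take a steep fall in pain as established. It rests on one 25-participant trial of a different corticosteroid, and the same Background section allows inflammation to persist or worsen.
- The plan that "PGI-I at days 1, 2 and 3 will use a mixed-effects repeated measures model" might look inconsistent with the handling of pain. It is not: PGI-I is analysed at three separate days, while the primary outcome is one summary per participant.

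A missing-at-random method is not a full answer either. If people stop because of current pain that is never recorded, it too is biased.

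**Conclusion.** The concern holds in a limited form. Carrying the last score forward has no fixed direction of bias here, and the unconditional label conservative is wrong. Under falling pain, the rule attenuates the effect when missingness is equal or higher on dexamethasone and can exaggerate it when placebo missingness is more than about 1.3 times as high. The 1.3 is specific to the cited falls; with equal falls the threshold is 1.

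The size is modest: roughly 0.7 to 1.4 points against a target difference of 10, and type I error of roughly 5.6% to 7.6%, for assumed gaps of 10 to 20 percentage points with the last score at T3 and SD 30. The article gives no missingness by arm. The figures shrink if last replies come later or pain levels off, and they could change if stopping depends on the participant's own pain. This should be fixed because it concerns the primary estimate and the remedy is cheap. It is not a fatal flaw.

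**What to change.** 1. Delete the bracketed description of the rule as conservative.
2. Make the primary handling a missing-at-random method that uses all observed scores. One option is to impute T1–T6 at score level by multiple imputation within arm, then compute the AUC in each completed data set. Useful predictors are the other pain scores, PGI-I at T2, T4 and T6, the recorded reply times and the covariates already listed. The alternative is a repeated-measures mixed model for T1–T6 with arm-by-time and baseline-by-time terms, reporting the AUC difference as a contrast.
3. Keep interpolation plus last observation carried forward as a sensitivity analysis.
4. Add a delta-based sensitivity analysis that shifts imputed scores separately by arm, because non-reply may depend on pain that was not recorded.

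The cost is wording in the protocol and analysis plan and some programming, settled before unblinding. No new data are needed. The drawback is a primary analysis that is slightly harder to describe.
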